### Recruitment

Participants with at least moderate depressive disorder are recruited from the inpatient, outpatient, and day clinic units of the Clinic of Child and Adolescent Psychiatry, Psychosomatics, and Psychotherapy at the University of Regensburg, Germany. Healthy controls are contacted via the residents’ registration office and through announcements on mailing lists and the department’s website. Interested individuals complete an initial eligibility screening via telephone. Figure 1 outlines the study timeline and potential dropout points.

**Fig. 1 Fig1:**
[figure not shown]
*Flow diagram.* MRI = Magnetic Resonance Imaging; T0 = telephone interview; T1 = first appointment; T2 = second appointment

### Study procedure

Prior to inclusion, potential participants complete a telephone screening (T0) to assess eligibility. The study involves two appointments. During the first appointment (T1, ~ 1.5 h), participants and their legal guardian receive detailed study information. After providing written informed consent, participants complete the Mini-International Neuropsychiatric Interview for Children and Adolescents (M.I.N.I-KID 6.0) and a battery of questionnaires (see Fig. 2).

**Fig. 2 Fig2:**
[figure not shown]
Study schedule. MIST = Montreal Imaging Stress Task; M.I.N.I.-KID 6.0 = Mini-International Neuropsychiatric Interview for Children and Adolescents; SPAIK = Social Phobia and Anxiety Inventory for Children; PAQ = Perth Alexithymia Questionnaire – German version; CTQ – SF = Child Trauma Questionnaire–Short Form; PDS = Pubertal Development Scale; NSSI = Non-Suicidal Self-Injury; ECR-RC = Experiences in Close Relationships Scale—Revised Child version; ERS = Emotion Reactivity Scale; EHI = Edinburgh Handedness Inventory; BAI = Beck Anxiety Inventory; BDI-II = Beck Depression Inventory-II; PANAS = Positive and Negative Affect Schedule; DSS-4 = Dissociation-Tension Scale; VAS = Visual Analogue Scale; OXT = Oxytocin, CORT = Cortisol; sAA = salivary α-amylase; T0 = telephone interview; T1 = first appointment; T2 = second appointment; T2a = Time previous to MIST, T2b = MIST, T2c = Time after MIST

The second appointment (T2) involves Magnetic Resonance Imaging (MRI) measurements and saliva collection for the analysis of OXT, CORT and sAA. T2 lasts approximately 2.5 h and begins with a 20-minute relaxation period, during which participants complete questionnaires and engage in non-stressful activities such as colouring, reading, or listening to music. Participants then complete a practise run of the Montreal Imaging Stress Task (MIST) to determine task difficulty and ensure familiarity before the scan.

rsFC MRI scans are conducted before and after stress induction. Functional MRI (fMRI) is used to measure brain activity during both control and stress conditions, while DTI assesses structural brain connectivity. During rsFC scans, participants fixate on a central fixation cross; during DTI, age-appropriate cartoons are shown to maintain engagement.

Saliva samples for OXT, CORT, and sAA are collected at multiple time points before and after stress exposure (see Fig. 3). Psychological states, including stress, anxiety, anger, shame, and guilt, are assessed using Visual Analogue Scales (VAS).

**Fig. 3 Fig3:**
[figure not shown]
Illustration of the experimental procedure of T2. RS = Resting State; fMRI = functional Magnetic Resonance Imaging; MIST = Montreal Imaging Stress Task; DTI = Diffusion Tensor Imaging; T1 & T2 = T1 & T2-weighted images. Saliva Samples are collected for measurement of oxytocin, cortisol and α-amylase

### MIST paradigm

A modified version of the MIST, a demanding mental arithmetic task adapted for fMRI, is employed to induce psychosocial stress [42]. The paradigm follows a block-design with two consecutive 8-minute scans: a Control MIST followed by a Stress MIST, each consisting of 54 trials. Trials lasts 6 s and are followed by a 1–3 s inter-trial interval displaying a fixation cross. Each trial features a unique math problem with multiple-choice answers (0–9), a response window of 0.5–5 s and 0.5 s of visual feedback (“Right,” “Wrong,” or “Time out”). Each scan concludes with a 14-second fixation cross (see Fig. 4). The fixed order, Control followed by Stress MIST, was chosen as it avoids carryover effects and reduces variability, enhancing the assessment of individual differences in the stress response.

Before scanning, participants complete practice problems to familiarize themselves with the task and determine difficulty. Problems range from easy (e.g., single-digit addition/subtraction) to hard (e.g., operations involving multiple double-digit numbers). Each participant’s difficulty level, based on practise response times, remains constant across both scans.

Before the Control scan, reassuring statements like, “It’s okay if you don’t answer all the math problems correctly.” aim to reduce participants’ stress. During this scan, participants are given sufficient time to respond (about 5 s per problem) and receive prerecorded positive auditory feedback (e.g., “You are doing great! Looks like you’ve got that under control! Good job!”).

Before the Stress scan, participants are informed that high accuracy is required and that their data may be excluded if performance is insufficient. They are told that previous participants answered over 80% of the questions correctly and that their data will only be included if they match this level. During the scan, they receive prerecorded negative feedback (e.g., “You are not doing as well as we had hoped. Please do your best to answer these correctly”). A performance bar appears at the top of the screen, comparing the participant’s performance (usually in the red zone) to an apparent group average (in the green zone) (see Fig. 4). To reinforce a sense of failure, the response window is dynamically adjusted using a stair-step procedure: it decreases by 0.5 s after a correct answer and increases by 0.5 s after an incorrect one, maintaining an average accuracy of ~ 50%. Response times range from 0.5 s to 5.0 s in 0.5-second increments. Following each response or timeout, a fixation cross is shown for 0.5–5 s, followed by 0.5 s of visual feedback (“Right,” “Wrong,” or “Time out”).

**Fig. 4 Fig4:**
[figure not shown]
Trial structure of the MIST stress scan. “FALSCH” is the German word for “WRONG”

Visual stimuli are presented using the Presentation Software (Neurobehavioral Systems, Inc.; Albany, CA, USA) and projected onto a translucent screen at the back of the scanner bore. Participants respond to arithmetic tasks using an MRI-compatible joystick, which triggers real-time visual feedback (“Right,” “Wrong,” or “Time out”). Prerecorded auditory feedback is presented through MRI-compatible headphones at four predetermined time points (i.e., after the first sets of nine trials) during each scan.

### Measurements

#### Psychological measures

All participants undergo the M.I.N.I. KID 6.0 [43], a structured clinical interview assessing DSM-IV and ICD-10 psychiatric disorders, to identify comorbid psychiatric disorders in the clinical groups or to confirm the absence of psychiatric diagnoses in healthy controls. Given evidence that childhood adversity can influence CORT responses to acute social stressors [44], retrospective assessment of maltreatment is conducted using the Childhood Trauma Questionnaire – Short Form (CTQ-SF) [45, 46]. The CTQ-SF is a validated 28-item measure covering sexual, emotional and physical abuse, and emotional and physical neglect. Items are rated on a five-point Likert scale (1 = “Never true”; 5 = “Very often true”). A recent meta-analysis supports its structural and construct validity [47].

Attachment anxiety and avoidance are measured with the German short version of the Experiences in Close Relationships Scale-Revised Child version (ECR-RC) [48, 49]. This self-report questionnaire includes 12 statements referring to participants’ relationship with their mother; six measuring attachment avoidance and six assessing attachment anxiety. Responses are rated on a seven-point Likert scale (1 = “strongly disagree”; 7 = “strongly agree”), with lower scores indicating higher attachment security. The ECR-RC has demonstrated excellent validity and reliability in youth samples [48]. Given that attachment patterns influence stress reactivity and OXT may modulate this relationship [50, 51], the ECR-RC was included to assess individual attachment differences in the context of OXT’s effects on stress.

Given the influence of handedness on lateralization [52], handedness is assessed using the Edinburgh Handedness Inventory (EHI; [53]). The inventory includes ten items assessing hand preference for specific tasks (e.g., drawing, eating with a spoon), from which a lateralization quotient (LQ) is calculated. Positive LQ values indicate right-handedness, while negative values reflect left-handedness.

Emotional reactivity is assessed using the Emotion Reactivity Scale (ERS), a 21-item self-report questionnaire for children and adolescents [54, 55]. The ERS assesses typical emotional response across interpersonal and situational contexts, including feelings of anger, sadness, and excitement. It includes three sub-dimensions: emotional sensitivity, intensity and persistence. Items are rated on a 5-point Likert scale (1 = “not at all like me”; 7 = “completely like me”), yielding a summed sore ranging from 0 to 84. The ERS has demonstrated excellent internal consistency (*α* = 0.94) and validity among adolescents [55].

Non-suicidal self-injury (NSSI) is assessed through self-report questions about participants’ NSSI history. Those reporting a positive history are asked about age of onset, most recent occurrence, and frequency of NSSI over their lifetime, past year, and past month.

Alexithymia is examined using the German version of the Perth Alexithymia Questionnaire, adapted for children and adolescents (PAQ-C) [56, 57]. This 24-item self-report measure is included to control for potential distortions in stress perception and reporting related to alexithymia. The PAQ-C assesses three subscales (difficulty identifying feelings, difficulty describing feelings, and externally oriented thinking) across both negative and positive emotions. Items are rated on a seven-point Likert scale (1 = “strongly disagree”; 7 = “strongly agree”), with higher scores indicating greater alexithymia. The PAQ has demonstrated strong psychometric properties across cultures [57–59].

Pubertal development is measured using the German version of the Pubertal Development Scale (PDS) [60, 61], a self-report questionnaire assessing physical maturation. Items assess developmental markers such as menarche, breast and pubic hair growth (females) and facial hair, voice changes, and pubic hair growth (males), relative to peers. Criterion validity and internal consistency measurements have demonstrated acceptable values [61]. Pubertal development influences CORT reactivity to acute psychosocial stress [62].

Social phobia is assessed using the German Screening for Social Phobia and Anxiety Inventory for Children (SPAIK) [63], based on DSM-IV criteria. The 26-item questionnaire covers psychological and physiological aspects of social phobia, with responses rated on a three-point Likert scale. The SPAIK has demonstrated strong cross-cultural validity and reliability in identifying social phobia in adolescents [64].

Anxiety symptoms are examined via the Beck Anxiety Inventory (BAI) [65, 66], a 21-item self-report scale measuring somatic and cognitive anxiety symptoms over the past seven days. The German version showed good psychometric properties, including strong convergent and divergent validity [67], and acceptable reliability in adolescent samples [68].

Depressive symptoms are assessed using the German version of the Beck Depression Inventory (BDI-II) [69, 70], a 21-item self-report scale for individuals aged 13 and older. Each item presents four statements of increasing severity, from which participants choose the one that applies most to them regarding the past two weeks. The German BDI-II shows excellent internal consistency (*α* ≥ 0.90), and reliability (>0.90), strong sensitivity to change, and good discriminative validity [71].

Dissociative states before and after neuroimaging are measured using the Dissociation-Tension Scale (DSS-4) [72], developed for repeated evaluations of state dissociation. It comprises four items (e.g., depersonalization, somatoform symptoms) rated on a 9-point Likert scale (0 = “not present”; 9 = “very strong”). The DSS-4 demonstrated good to excellent psychometric properties, including internal consistency, reliability, differential and convergent validity [72].

Participants’ current affective state during relaxation periods before and after the MRI is assessed using the German version of the Positive and Negative Affect Schedule (PANAS) [73, 74]. This 20-item self-report questionnaire comprises ten items each for positive (e.g., “enthusiastic,” “inspired”) and negative affect (e.g., “upset,” “ashamed”), rated on a 5-point Likert scale (1 = “not at all”; 5 = “extremely”). The German PANAS showed good psychometric properties [73].

Further, using Visual Analogue Scales (VAS) [75] (1 = “not at all”; 10 = “extremely”) participants are asked about how stressed, anxious, angry, ashamed, and guilty they feel at nine different time points throughout T2 (see Fig. 3). VAS are particularly suitable for assessing subjectively experienced stress, as they have been shown to be both reliable [76] and valid [77].

#### Saliva sampling

To analyse peripheral OXT, CORT and sAA levels, saliva samples are collected at eight time points using Salivettes^®^ (Sarstedt, Nümbrecht, Germany; item number 51.1534.500) following a standardized protocol [78]. Samples are stored at -20 °C until biochemical analysis. Salivary OXT will be analysed by radioimmunoassay (RIAgnosis, Sinzing, Germany). Salivary CORT and sAA will be quantified at the Department of Biopsychology, Technical University of Dresden, Germany.

#### Physiological consistency of measurement

All measurements are conducted on weekdays, with the experimental session (T2) scheduled exclusively in the afternoon to minimize circadian influences on hormone levels [79, 80]. For post-menarcheal females not using contraceptives, T2 is scheduled during the luteal phase (estimated based on self-reported cycle length, menstruation duration, and the date of last menstrual onset) to ensure comparability of CORT reactivity across sexes [81, 82]. Although no significant sex differences in OXT levels have been reported in adolescents [83], oral contraceptive use is assessed and statistically controlled, given evidence that such use blunts CORT reactivity [84]. Participants are instructed to refrain from eating and to only drink water two hours before and during T2, with compliance confirmed via self-report.

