### Hypotheses

We expect blunted CORT and OXT stress responses in adolescents with MDD (with or without comorbid anxiety) relative to healthy controls, whereas baseline levels of these hormones are not expected to differ systematically across groups. For rsFC, we hypothesize time (pre- vs. post-stress) × group (MDD, COM, HC) interactions within fronto-limbic circuits, with greater alterations in adolescents with depressive disorders compared to healthy controls. Exploratorily, we expect that youth with MDD and comorbid anxiety will show more pronounced endocrine blunting and stronger fronto-limbic rsFC alterations than those with MDD alone. Finally, we hypothesize that stress-induced fronto-limbic rsFC changes will be significantly associated with endocrine reactivity (CORT, OXT, sAA), reflecting shared neuroendocrine mechanisms of stress adaptation.

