The second primary outcome is hormonal reactivity. We hypothesize that stress exposure will elicit group differences in OXT, CORT and sAA. Raw hormonal values will be square-root transformed to reduce skewness [93]. Reactivity will be quantified using area under the curve (AUC) [94] with respect to increase (AUC_i_) and ground (AUC_g_), as well as delta scores reflecting change from baseline to peak, peak to recovery, and recovery magnitude [95–97]. Repeated-measures ANOVAs will examine the interaction between time (baseline, peak, recovery; within-subject factor) and group (between-subject factor), controlling for sex, age, and pubertal status. False Discovery Rate (FDR) correction will be applied across hormonal outcomes and indices. Subjective stress ratings assessed with VAS will be analysed in parallel, using repeated-measures ANOVAs with the same model structure.

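### The hormone models omit the clock time of T2, leaving baseline cortisol and AUC_g open to confounding if start times differ by group

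*Protocol article*

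**What the plan says.** Physiological consistency of measurement puts all measurements on weekdays, "with the experimental session (T2) scheduled exclusively in the afternoon to minimize circadian influences on hormone levels". According to Study procedure, "T2 lasts approximately 2.5 h and begins with a 20-minute relaxation period". The same section on physiological consistency says that oral contraceptive use will be adjusted for statistically; time of day gets no such adjustment.

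Primary outcomes sets the hormone analysis: repeated-measures ANOVAs with time (baseline, peak, recovery) as the within-subject factor and "group (between-subject factor), controlling for sex, age, and pubertal status". The reactivity indices are areas under the curve "with respect to increase (AUC_i_) and ground (AUC_g_), as well as delta scores reflecting change from baseline to peak", and further deltas. AUC_g is therefore a named index of the second primary outcome.

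Table 1 matches controls on sex and age and names four more factors to be controlled for; session time is not among them. Under Recruitment, patients "are recruited from the inpatient, outpatient, and day clinic units" of one university department, while controls are approached through the population register and by advertisement. Hypotheses predicts blunted cortisol and oxytocin responses in patients and adds that "baseline levels of these hormones are not expected to differ systematically across groups".

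**The concern.** Restricting T2 to the afternoon narrows the diurnal range but does not remove it, because levels can still change across the afternoon. Whether that matters for group comparisons depends on whether the groups start at the same time on average. The two recruitment routes make a difference possible, and nothing in the stated matching or modelling would prevent it or correct for it.

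At stake are the measures that carry absolute level. If controls were tested later while cortisol is falling, their baseline and AUC_g would be understated. That would hide patient blunting on AUC_g, or produce a baseline difference that Hypotheses does not expect. If controls were tested earlier, the sign would reverse. Baseline cortisol is also a predictor alongside group in the first regression under Secondary outcomes, so a level shift would reach that model too.

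**Working it through.** The article gives no figure for diurnal slope or start times, so there is no number of the plan's own to reproduce on this point.

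**Inputs from the article.** Three groups of 30 (N = 90); α = 0.05; T2 lasting about 2.5 h in the afternoon; hormone covariates sex, age and pubertal status.

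**Assumptions, not in the article.** Mean start time differs by *h* = 0 to 2 h between controls and both patient groups. The level falls linearly by *s* = 0.05 to 0.3 SD per hour on the analysed scale. There is no true group difference.

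**Step 1: which indices are exposed.** Let person *i* start at clock time T and have level y(t) = a − s(T + t) + r(t) at t hours into a session of length L.
- Baseline: y(0) = a − sT + r(0), which contains T.
- AUC_g = ∫y = aL − sTL − sL²/2 + ∫r, which contains T.
- AUC_i = AUC_g − L·y(0) = −sL²/2 + ∫r − L·r(0). T has cancelled.
- Delta: y(t) − y(0) = −st + r(t) − r(0). T has cancelled.

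Under a linear trend, start time enters baseline, AUC_g and the group main effect, but not AUC_i, the deltas or time × group. With a curved decline the cancellation would be incomplete.

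**Step 2: size of the spurious shift.** d = h × s. With group means (0, d, d), f = d·√2/3, and the noncentrality of the three-group F test is λ = N·f² = 90 × (2/9)d² = 20d². Example: h = 1 h and s = 0.2 give d = 0.20, λ = 0.8 and rejection in 11.3% of trials.

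Rejection rate of the unadjusted three-group level test (nominal 5%):

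| Shift h | s = 0.05 | s = 0.1 | s = 0.2 | s = 0.3 |
|---|---|---|---|---|
| 0 h | 5.0% | 5.0% | 5.0% | 5.0% |
| 0.5 h | 5.1% | 5.4% | 6.5% | 8.4% |
| 1 h | 5.4% | 6.5% | 11.3% | 20.1% |
| 1.5 h | 5.8% | 8.4% | 20.1% | 40.7% |
| 2 h | 6.5% | 11.3% | 33.0% | 65.2% |

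These are single tests before the planned FDR correction, which would lower the rates, and without the planned covariates.

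**Step 3: does the covariate work?** A simulation used 1,000 runs per cell, within-group start-time SD 0.75 h, h = 0 to 1.5 h and s = 0.1 to 0.3.
- Baseline, unadjusted, at h = 1 h: 6.6%, 12.0% and 19.7% for s = 0.1, 0.2 and 0.3, in line with the table.
- Baseline, with clock time as covariate: 4.1% to 6.1% in every cell.
- Change score, unadjusted: 3.4% to 5.8% in every cell, as Step 1 predicts.

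**Step 4: precision without any imbalance.** If the afternoon is taken as 12:00 to 18:00 (assumption), a 2.5 h session leaves a start window of 6 − 2.5 = 3.5 h. Uniform starts have SD 3.5/√12 ≈ 1.0 h. At s = 0.2 the added variance in level measures is (0.2 × 1.0)² = 0.04, about 4% of the person-level variance.

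**The case against.** The strongest reply is that bias needs a group difference in start time and the article documents none. Recruitment names sources, not daily schedules; the patient pool includes outpatients, and Table 1 treats schooling as relevant to participants generally. This stands. A reader might infer that patients are tested early and school-going controls late, but that is conjecture, and with no shift the level test holds at 5% whatever the slope.

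It is also fair that the afternoon restriction already handles part of the problem, and that exact appointment slots may sit in the full protocol. The absence of a printed start window is therefore not the point, and the article does not support reading it as permission to start at any hour of the afternoon. What remains is that the covariate list and the matching factors are stated, and neither includes time of day.

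Thirdly, the main hormone hypothesis concerns blunted responses, and the ANOVAs examine time × group. Those targets are largely unaffected under a linear trend. Moreover, later-tested controls with falling cortisol would work against a finding of blunting on AUC_g, not for it. Both points stand and confine the concern to level measures.

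Finally, the large rates in the table are extreme cases. A 2 h gap in means is about two SDs of the assumed 3.5 h window, close to separating the groups altogether. Those rows should not be taken as what to expect.

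**Conclusion.** The point holds as a gap in protection, not as an error or a demonstrated bias. The article names circadian influence as a threat, narrows it by scheduling, and then specifies hormone models and matching that leave the remainder unadjusted. If mean start times differ by group, baseline cortisol, AUC_g and the group main effect can show a false difference or hide a real one. The false-positive rate is about 5 to 8% for a 0.5 h gap and about 5 to 20% for a 1 h gap, against 5% with no gap. Without imbalance the only cost is a little extra variance, about 4% in the example.

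These sizes rest on assumed slopes and start-time gaps. The sign is argued for cortisol only, on the assumption that it falls through the afternoon; the article gives no direction or slope for any of the three markers. A reader might infer that the primary reactivity findings are in danger; the calculations do not support that, since AUC_i, the deltas and time × group stay near 5% without adjustment. The change is a cheap improvement.

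**What to change.** Record the clock time of the first saliva sample at T2. Add it as a covariate in the hormone models under Primary outcomes, at least for baseline level, AUC_g and the group main effect. Report start times by group. Where scheduling allows, balance start times across the three groups while sessions are still being booked; this is safer than adjustment alone, which leans on a linear slope and loses precision if the groups hardly overlap. A clock-time × time interaction is optional, as a sensitivity analysis for the change indices.

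The cost is about one degree of freedom with 90 participants, one timestamp per session and minor scheduling effort.
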